### **3.3. Data collection and analysis**

#### **3.3.1. Data collection methods**

##### **a. Data collection technique**

Data collection will consist of taking the psychomotor development assessment test. For the present study, it is the test “Age, Stage and Questionnaires 3rd edition”, ASQ3 which will be used.

##### **Taking the test**

The test will take place in two stages:

- Observation of the realization of the activities by the child. These are 5 different items relating to:
  - Communication (language);
  - Motor skills (fine and gross);
  - Problem solving (cognition);
  - Individual or social skills (sociability).
- Complement of the test with the completion of a questionnaire of 30 items by the mother or the accompanying person.

##### **Duration and pace of the assessment**

For each participant, the test lasts between 10 to 15 minutes maximum. Each child will undergo three assessments, one on admission, one at discharge in the third month (exit from treatment for children declared cured) and one in the sixth month.

##### **Data logging**

The activities carried out by each participant are recorded in a summary results sheet allowing rapid interpretation.

Questionnaires are managed and corrected using the ASQ Web-Based® Screening software available online.

##### **b. Data collection plan**

##### ***Staff recruitment and training***

The study must be organized in conditions as close as possible to road practice. As a result, the providers assigned to taking anthropometric measurements will also be responsible for evaluating the psychomotor development of each participant.

These providers will be trained by the psychomotor therapist in order to become familiar with the use of ASQ3 and the assessment of the psychomotor development of the participants.

### **c. Organization of the collection**

Depending on the sampling interval, when a child meets the inclusion criteria, immediately after taking anthropometric measurements, providers assess their psychomotor development.

The assessment will be done on admission, after recovery and then once every six months until the end of the study. Even if they are declared cured and they no longer come to UNTA, providers will keep contact details on their addresses in order to continue DPM assessments.

### **3.3.2. Data analysis**

Descriptive analysis (percentage, medians with interquartile space and extremes, means plus or minus standard deviation) will be performed for categorical data.

The chi-square test will be used for the comparison of proportions and the Student's t-test to compare the means in the two groups.

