### **2.3.3. Statistical analyzes**

For the quantitative part of the study, the data will be summarized in Mean and Standard Deviation if they are normally distributed (normality test) for continuous variables and in absolute and relative frequencies for categorical variables.

The t-test and the chi-square test will be used respectively to compare the means and the proportions of the socio-demographic characteristics at admission for the quantitative and qualitative variables.

Linear regression analyzes will be used to determine the significant differences between the 2 groups of children for the quantitative variables.

Binary logistic regression analyzes will be used to determine the significant differences between the 2 groups of children for the binomial qualitative variables (2 response modalities).

Multinomial logistic regression analyzes will be used to determine the significant differences between the 2 groups of children for the multinomial qualitative variables (3 or more modalities).

All analyzes will be done in an adjusted and unadjusted model and a difference is statistically significant when the P-value is less than 0.05.

The results will be analyzed using statistical software, in this case STATA, version 17.

The main analyzes will be done by intention to treat (ITT) and per protocol for the main result, in this case, the speed of weight gain. The other secondary results will be analyzed only by intention to treat (ITT).

For the DPM, a score will be assigned to the participant and the sum will constitute the total score for each participant per domain.

For focus group data, after transcription of the recordings into Word 2019, thematic analysis will be done using Excel tables (matrix) or Nvivo® software.

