### 3.1.3. Expected results

- **Prevalence of psychomotor developmental delay:** assess the skills and abilities acquired in each of the 4 domains of DPM (Motor skills, language, cognition and sociability);
- **Evolution of psychomotor development according to the dose of RUTF received:** compare the improvement in the acquisition of skills and abilities acquired in each of 4 areas of DPM according to the dose of RUTF received according to the trial protocol.

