### 3.1.4. Sample size

$$n = t^2 \times p \times (1-p) / m^2$$

- *n: Minimum sample size to obtain significant results for an event and a fixed level of risk*
- *t: Confidence level (the typical value of the 95% confidence level will be 1.96)*
- *p: estimated proportion of the population exhibiting the characteristic studied (0.50 is considered if p is unknown);*
- *m: Margin of error (generally set at 5%).*

Applying the above formula, the minimum sample for this study is 384 children. After rounding up, a total of 400 children will be included in the study on psychomotor development, including 200 in the intervention group (reduced dose) and 200 in the control group (standard dose).

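### Annex 3 and section 2.3.3 give different methods for comparing psychomotor outcomes between arms, and neither names the admission score as a covariate or says which result is primary

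*Protocol*

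**What the plan says.** Annex 3 of the protocol is a sub-study with its own objectives, sample size and analysis section. For the arm comparison, section 3.3.2 states: "The chi-square test will be used for the comparison of proportions and the Student's t-test to compare the means in the two groups". It names no covariate and does not say whether the t-test is applied to follow-up scores or to change from admission.

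The same annex sets up repeated measurement: "Each child will undergo three assessments, one on admission", the others being at discharge and in the sixth month. Its section 3.1.3 describes the aim as to "compare the improvement in the acquisition of skills and abilities acquired in each of 4 areas of DPM" according to dose. The size is 400 children, "including 200 in the intervention group (reduced dose) and 200 in the control group (standard dose").

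Section 2.3.3 of the main text sets linear regression for quantitative outcomes and logistic regression for binary ones. It requires all analyses in an adjusted and an unadjusted form. There, the t-test and chi-square are reserved for socio-demographic characteristics at admission. The section does include the psychomotor outcome, but its only specific sentence concerns scoring: "For the DPM, a score will be assigned to the participant and the sum will constitute the total score" per domain. It lists no adjustment covariates and does not say which of the two models is primary.

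Section 2.2.1 blocks the randomization within each of the 14 UNTAs, and section 2.1.7 records age at admission.

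**The concern.** Two sections of one document prescribe different analyses of the same outcome. An analyst could follow Annex 3 and report a t-test, or follow section 2.3.3 and report regression with or without covariates, and would comply with the protocol either way. With no primary result named, the choice could be made after the data are seen.

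The second issue is efficiency. The hypothesis in the main text is that the two arms have the same psychomotor development, so the width of the interval on the arm difference decides what the sub-study can conclude. The admission score is collected anyway. If it correlates with the later score, leaving it out discards precision that costs nothing to keep. The sub-study was also not sized for the arm comparison, as the working shows.

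**Working it through.** **The plan's own figure.** Annex 3 section 3.1.4 uses n = t² × p × (1 − p) / m², with t = 1.96 ("the typical value of the 95% confidence level will be 1.96"), p = 0.50 ("0.50 is considered if p is unknown") and m = 0.05.

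- n = 1.96² × 0.25 / 0.0025 = 384.16, which agrees with the text: "the minimum sample for this study is 384 children".
- This is the precision of one overall prevalence (±5 points). It is not a power calculation for two arms, and it includes no allowance for loss.

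**Inputs for the arm comparison.** 200 per arm (Annex 3 section 3.1.4), two-sided 5% (section 2.3.3) and 80% power (the level used for the main trial in section 2.1.6). The admission-to-follow-up correlation r is not in the protocol, so 0.3, 0.5 and 0.7 are assumptions that show a range. The calculation uses the normal approximation, in SD units, with equal SD at both times.

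**Unadjusted t-test on the follow-up score.** Detectable difference = (1.960 + 0.842) × √(2/200) = 2.802 × 0.1 = 0.280 SD.

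**Linear regression with the admission score (ANCOVA).** The variance is multiplied by 1 − r², so the detectable difference is 0.280 × √(1 − r²) and the equivalent number per arm is 200 / (1 − r²).

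- r = 0.3: 0.267 SD; 200 / 0.91 ≈ 220 per arm
- r = 0.5: 0.243 SD; 200 / 0.75 ≈ 267 per arm
- r = 0.7: 0.200 SD; 200 / 0.51 ≈ 392 per arm

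Power for a true difference of 0.25 SD is 70.5% unadjusted, against 74.6%, 82.3% and 93.8% adjusted.

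**If the t-test is on change instead.** The variance of change is 2(1 − r), so the detectable difference is 0.280 × √(2(1 − r)): 0.331, 0.280 and 0.217 SD at r = 0.3, 0.5 and 0.7. The ratio of ANCOVA variance to change-score variance is (1 − r²) / (2(1 − r)) = (1 + r)/2.

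- r = 0.5: 200 / 0.75 ≈ 267 per arm
- r = 0.7: 200 / 0.85 ≈ 235 per arm

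The gain over a change-score test therefore shrinks as r rises.

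**With losses.** Assuming the main trial's 20% dropout (section 2.1.6) also applies here, 200 × 0.8 = 160 per arm. The detectable difference is then 0.313 SD unadjusted and 0.271 SD with ANCOVA at r = 0.5.

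**Binary delay outcome.** At 200 per arm and a proportion of 0.5, the unadjusted 95% half-width on a risk difference is 1.96 × √(2 × 0.25/200) = 9.8 points. The chi-square has 80% power for an increase of about 12 points from a control rate of 20%, and about 14 points from 50%. The factor 1 − r² does not apply to this outcome, so no gain is computed for it.

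**The case against.** The strongest reply is that section 2.3.3 already promises adjusted regression for all analyses and mentions the psychomotor score, so what is missing is only a covariate list, which a SAP may supply. The first half stands. A reader who looks only at Annex 3 might infer that the psychomotor comparison is planned as unadjusted only, and the protocol as a whole does not support that. The second half does not dispose of the point. No rule says which section prevails, and a conflict between two methods stated in the protocol is not detail deferred to a SAP.

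A second reply is that a t-test on change would already use the admission score, and the stated aim of comparing improvement fits that reading. This is fair: Annex 3 leaves it open, so it cannot be said that the planned test ignores the admission score. It also means that the 392 per arm cannot be quoted alone, because against a change-score test the figure at r = 0.7 is 235.

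A third reply is that adding covariates to a logistic model generally does not narrow the interval on the log odds ratio, and it changes the estimand to a conditional odds ratio. That is correct. It is why the figures here are confined to the continuous scores, and why the fix asks for a standardized risk difference.

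Finally, the arms are individually randomized, so omitting the covariate does not in itself bias the comparison. That stands.

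**Conclusion.** The point holds as an inconsistency with a precision cost. Annex 3 section 3.3.2 and section 2.3.3 give different methods for the same outcome, and neither names the admission score as a covariate or identifies the primary result.

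The benefit of baseline adjustment is positive for any r above 0 against a follow-up-score test, and for any r below 1 against a change-score test. Its size rests on an assumed r. It is modest at r = 0.3 against a follow-up-score test (9% of the variance) and substantial at r = 0.7 (49%). Against a change-score test it is 25% at r = 0.5 and 15% at r = 0.7.

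A reader might go further and infer that the psychomotor comparison is biased, or that the delay proportions would gain by the same factor. Neither follows. The matter is efficiency, and an unresolved choice of method, in a secondary-outcome sub-study.

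**What to change.** In Annex 3 section 3.3.2, replace the t-test and chi-square for the arm comparison with the regression of section 2.3.3, and state that the baseline-adjusted model is primary:

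- **Domain scores:** linear regression of each score, at discharge and at six months, on arm, admission score, age and UNTA. Report the mean difference with its 95% CI.
- **Delay:** logistic regression on arm, admission delay status, age and UNTA. Report a standardized risk difference with its 95% CI.

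The unadjusted result can stay as a supporting analysis, which keeps the promise in section 2.3.3 of both forms. A cross-reference from section 2.3.3 to Annex 3 would prevent the two from diverging again. The cost is a few sentences. Admission score, age and UNTA are already recorded, so no new data are needed.

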#### **4) Secondary outcomes**

- **Acceptance** of a reduced dose during SAM treatment by healthcare staff as well as the community: this involves assessing the perceptions of families and healthcare providers on the amount of RUTF received, consumption practices and 'uses and their attitude to dose reduction.
- **The relapse rate:** this is the proportion of children in care for SAM and declared cured who become SAM again in the 3 months after the end of treatment.
- **Psychomotor development :** This sub-study aims to assess the proportion of children with psychomotor developmental delay (DPM) and to monitor their progress during treatment. Psychomotor Developmental Delay (RDPM) is understood to mean disorders in the acquisition of skills and competences in the areas of language, cognitive, motor and social interaction. The RDPM corresponds to a score of less than 70% in two of the four domains of the DPM(34). For this sub-study, it is expected that the MPD of children with RDPM will improve after their management.(35) (36) (37) due to the simple fact of the medical and nutritional intervention without particular action on the DPM during the treatment.

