The practical modalities of the DPM evaluation as well as the corresponding items are given in the appendix to this protocol (appendix 3).

For the children who will be selected for the Sub-study on psychomotor development, their anthropometric measurements (weight, height, MUAC, search for edema) will be taken during a visit after treatment when they respond to the appointments for the evaluation of the patient. psychomotor development: at the end of treatment (for children declared cured) then at six months. This information will be noted in their corresponding individual monitoring sheet.

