## **2. Goals**

a. Main objective

Contribute to improving the overall care of children with SAM without medical complications by integrating aspects of psychomotor development.

b. Specific objectives

The specific objectives of this study are:

- To determine the prevalence of RDPM in SAM children without medical complications in the ZS of Nzaba and Bonzola in the province of Kasai Oriental in the DRC;
- Evaluate the evolution of psychomotor development in SAM children without medical complications in the ZS of Nzaba and Bonzola in the province of Kasai Oriental in the DRC;

To compare psychomotor development in SAM children without medical complications as a function of the dose of RUTF received in the ZS of Nzaba and Bonzola in the province of Kasai Oriental in the DRC.

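### Annex 3 sets change in psychomotor development over time as an objective, but every analysis it names compares independent groups and none fits change within the same children

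*Protocol*

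**What the plan says.** Annex 3, section 2 (Goals), gives three specific objectives: prevalence of delay, change over time, and comparison by dose. The second reads "Evaluate the evolution of psychomotor development in SAM children without medical complications" and is separate from the dose comparison. Section 2.1.4 of the main protocol, under secondary outcomes, adds a direction: "it is expected that the MPD of children with RDPM will improve after their management".

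The same children are measured repeatedly. Annex 3, on the duration and pace of the assessment, says "Each child will undergo three assessments, one on admission, one at discharge in the third month", with a third in the sixth month. Annex 3, section 3.3.1 c, describes the timing differently: "The assessment will be done on admission, after recovery and then once every six months until the end of the study". Section 2.3.1 f of the main protocol (At UNTA level) places the post-treatment visits "at the end of treatment (for children declared cured) then at six months".

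For the analysis, Annex 3, section 3.3.2, announces descriptive summaries and then: "The chi-square test will be used for the comparison of proportions and the Student's t-test to compare the means in the two groups". Section 2.3.3 of the main protocol adds linear, binary logistic and multinomial regression, adjusted and unadjusted, each for differences between the two groups. Annex 3, section 3.1.3, lists a between-arm result on change: "compare the improvement in the acquisition of skills and abilities acquired in each of 4 areas of DPM", according to the dose received.

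**The concern.** How children change from admission to discharge to six months is a question about repeated results on the same child. The chi-square test and the two-group t-test assume independent observations, and the regressions are specified only between arms. No paired test, change score or repeated-measures model appears for the second objective. Whoever follows section 3.3.2 must either leave that objective untested or apply a method that treats one child's results as coming from different children.

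Two things are then at stake. Ignoring the positive correlation between a child's own results makes the standard error of the change too large, so a real change is more easily missed. And an unpaired before/after comparison takes everyone tested at admission against whoever is tested later, which by design at discharge means children declared cured. If the children who drop out of the comparison were more often delayed at admission, the described prevalence falls without any child improving, and improvement is what the protocol expects to see.

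**Working it through.** **The plan's own figure.** Annex 3, section 3.1.4, uses n = t²p(1−p)/m² with t = 1.96, p = 0.50, m = 0.05: 3.8416 × 0.25 / 0.0025 = 384.16, which matches the stated 384, rounded up to 400 (200 per arm). This sizes one prevalence at one time, not a change.

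**Inputs.** From the documents: n = 400 and significance at 0.05 (taken as two-sided). The 20% loss is borrowed from the main trial's dropout allowance in section 2.1.6; Annex 3 states none of its own. Not in the documents, so assumed and shown as ranges: the within-child correlation r, the prevalence of delay, the size of the change, and how strongly loss is related to delay.

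**Standard error of a mean change** (SD = 1, both visits complete). Treated as independent: √(2/400) = 0.0707. Paired: √(2(1−r)/400). The ratio is 1/√(1−r), and the true type I error of the independent test at nominal 0.05 is 2(1 − Φ(1.96 × ratio)). Power for an assumed change of 0.15 SD is Φ((0.15 − 1.96 × 0.0707)/SE paired) for the independent test and Φ(0.15/SE paired − 1.96) for the paired test.

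| r | SE independent | SE paired | ratio | true type I error | power, independent | power, paired |
|---|---|---|---|---|---|---|
| 0.3 | 0.0707 | 0.0592 | 1.20 | 0.019 | 58% | 72% |
| 0.5 | 0.0707 | 0.0500 | 1.41 | 0.006 | 59% | 85% |
| 0.7 | 0.0707 | 0.0387 | 1.83 | 0.0003 | 62% | 97% |

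**Proportions.** Assume delay falls from 30% to 24% in 400 children with r = 0.5.
- Unpaired SE = √((0.21 + 0.1824)/400) = 0.0313; z = 0.06/0.0313 = 1.92, p = 0.055; power about 48%.
- Paired SE = √((0.21 + 0.1824 − 2 × 0.5 × √(0.21 × 0.1824))/400) = 0.0222; z = 2.71, p = 0.007; power Φ(2.71 − 1.96), about 77%.

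This effect happens to put the two tests on either side of 0.05. With an assumed 40% to 35% the chi-square z is 1.46 and McNemar's z is 1.74, 2.06 and 2.65 at r = 0.3, 0.5 and 0.7: the same direction, but not always a different conclusion.

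**Composition.** Let no child change, and let 20% not be retested. The prevalence among those retested is prevalence × (1 − loss in delayed children)/0.8. At 30% prevalence at admission:
- loss odds ratio 1.5 (24.7% of delayed children lost): 0.30 × 0.753/0.8 = 28.2%, a fall of 1.8 points;
- odds ratio 2 (28.3% lost): 0.30 × 0.717/0.8 = 26.9%, a fall of 3.1 points;
- odds ratio 3 (33.3% lost): 0.30 × 0.667/0.8 = 25.0%, a fall of 5.0 points.

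Across admission prevalences of 30% to 50% the fall is about 2 to 5 points, and the unpaired chi-square gives z of 0.52 to 1.49, below 1.96. Only at the extreme of the grid, 30% lost with odds ratio 3, is the fall 7.2 to 8.0 points with z of 2.04 to 2.12.

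**The case against.** The strongest reply is that the quoted sentence is a between-arm plan. The t-test is stated for the two groups, and nothing in the protocol expressly applies either test across visits. This stands. A reader might infer that the protocol prescribes a wrong variance for the change, but the text does not say so; the error arises only if the named tests are used over time.

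Second, Annex 3, section 3.1.3, frames change partly as a comparison by dose. A two-sample test at a visit, or on each child's change, treats the arms as the independent groups that they are. A reader might infer that the dose comparison is invalid too; the documents do not support that.

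Third, the variance error is conservative, and the composition shift would usually not be declared significant. For example, if 20% were lost and 45% of those were delayed at admission against 30% overall, the later figure would be (120 − 36)/320 = 26.25%. The unpaired test of 30.0% against 26.25% gives 0.0375/√(0.21/400 + 0.1936/320) = 1.12. The tempting reading that dropout would produce a false finding of improvement therefore goes too far. It would produce a misleading description. Section 3.3.1 c also plans to keep addresses so that assessment can continue after cure, which may limit loss at six months.

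Fourth, a within-child model is the kind of detail often left to a statistical analysis plan. This does not dispose of the point, because section 3.3.2 is not silent. It names tests, its chi-square clause covers comparison of proportions without restriction, and those tests do not fit one of the three objectives. A plan written to follow it would inherit the mismatch.

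**Conclusion.** The point holds for the change-over-time objective only. The protocol sets that objective, measures the same children repeatedly, and names only methods for independent groups. The between-arm comparisons are not affected.

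If the named tests were used across visits, the standard error would be about 1.2 to 1.8 times too large for correlations of 0.3 to 0.7. This loses power and does not inflate false positives. The described prevalence could also shift by about 2 to 5 points at 20% loss, on the condition that loss is related to delay (odds ratio 1.5 to 3) and that different sets of children are compared. Correlation, prevalence, effect and loss pattern are all assumptions. The mismatch between objective and tests, and the restriction of the discharge assessment to cured children, come from the text itself. The change should be made, but it does not bear on the trial's primary result.

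**What to change.** In Annex 3, section 3.3.2:
- Analyse change over time with one repeated-measures model per outcome: a linear mixed model for scores, and GEE or a mixed logistic model for delay, with visit, arm, visit-by-arm and allowance for repeated results on the same child (a child effect, or clustering by child in GEE).
- At minimum, use McNemar's test and the paired t-test in children with both assessments, and report those children's own admission values beside the later ones.
- Keep the two-sample tests for comparisons between arms, including the between-arm comparison of change, adjusted for the admission score.
- State that results at discharge refer to children declared cured. Pairing removes the mixing of different children but not this restriction.

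Reconcile the two accounts of the schedule in Annex 3 (a single assessment in the sixth month, or one every six months until the study ends), since they imply different numbers of repeated measures.

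The cost is wording only. The plan already collects these assessments and gives each child a unique identifier by which they can be linked.
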